## Abstract

**Background:**

Go Nisha Go™ (GNG), is a mobile game combining behavioural science, human-centric design, game-based learning, and interactive storytelling. The model uses a direct-to-consumer (DTC) approach to deliver information, products, services, interactive learning, and agency-building experiences directly to girls. The game’s five episodes focus on issues of menstrual health management, fertility awareness, consent, contraception, and negotiation for delay of marriage and career. The game’s effectiveness on indicators linked to these issues will be measured using an encouragement design in a randomized controlled trial (RCT).

**Methods:**

A two-arm RCT will be conducted in three cities in India: Patna, Jaipur, and Delhi-NCR. The first arm is the treatment (encouragement) arm (n = 975) where the participants will be encouraged to download and play the game, and the second arm (n = 975) where the participants will not receive any nudges/encouragement to play the game. They may or may not have access to the game. After the baseline recruitment, participants will be randomly assigned to these two arms across the three locations. Participants of the treatment/encouragement arm will receive continuous support as part of the encouragement design to adopt, install the game from the Google Play Store at no cost, and play all levels on their Android devices. The encouragement activity will continue for ten weeks, during which participants will receive creative messages via weekly phone calls and WhatsApp messages. We will conduct the follow-up survey with all the participants (n = 1950) from the baseline survey after ten weeks of exposure. We will conduct 60 in-depth qualitative interviews (20 at each location) with a sub-sample of the participants from the encouragement arm to augment the quantitative surveys.

**Discussion:**

Following pre-testing of survey tools for feasibility of methodologies, we will recruit participants, randomize, collect baseline data, execute the encouragement design, and conduct the follow-up survey with eligible adolescents as written in the study protocol. Our study will add insights for the implementation of an encouragement design in RCTs with adolescent girls in the spectrum of game-based learning on sexual and reproductive health in India. Our study will provide evidence to support the outcome evaluation of the digital mobile game app, GNG. To our knowledge this is the first ever outcome evaluation study for a game-based application, and this study is expected to facilitate scalability of a direct-to-consumer approach to improve adolescent sexual and reproductive health outcomes in India.

*Trial registration number:* ctri.nic.in: CTRI/2023/03/050447.

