#### Randomization

For implementation of the RCT we will prepare the eligible list of participants after household screening, followed by individually randomizing the total participants into control and intervention groups [15]. Randomized participants in the treatment arm will get exposure to the GNG game as part of the encouragement design, while the participants randomly assigned to the control arm will not get any additional encouragement to download or play the game. (See Fig. 1) Researchers will not be blinded to the treatment condition assigned to individual participants [16].

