#### Timepoint for tracking encouragements for participants

We will follow up with the participants by using a tracking sheet. Please see Table 2 for the schedule of enrollment,  implementation of encouragement, and assessments.

**Table 2 Tab2:** Schedule of enrolment, intervention, and assessment

Timepoint**	Study period*			
	Enrollment	Allocation	Post-allocation	
	−t_1_	0	t_1_	t_2_
Enrolment				
Eligibility screen	X			
Informed consent	X		X	X
Allocation		X		
Interventions: [Intervention: GNG game encouragement design]			↔	﻿↔
Control: No Encouragement				
Assessments: Baseline variables – indicators (see Table 3)			X	
Menstrual hygiene			X	X
Contraception			X	X
Agency (decision-making, negotiation, and consent)			X	X

*Recommended content can be displayed using various schematic formats. See SPIRIT 2013 Explanation and Elaboration for examples from protocols

**List specific timepoints in this row

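### The article contradicts itself on whether the baseline survey precedes randomisation; a baseline taken after allocation can bias the primary difference-in-differences estimate

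*Protocol article*

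**What the plan says.** Four places in the protocol article bear on the order of baseline survey and allocation.

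- **Abstract, Discussion** is explicit that the baseline follows randomisation and precedes encouragement: "we will recruit participants, randomize, collect baseline data, execute the encouragement design, and conduct the follow-up survey".
- **Table 2** (schedule of enrolment, intervention and assessment) puts allocation at time 0. The row "Baseline variables – indicators (see Table 3") has its only mark at t1, under the post-allocation heading. Informed consent is marked at enrolment and again at t1 and t2. The row "Interventions: [Intervention: GNG game encouragement design" has arrows at t1 and t2, so baseline and encouragement share the t1 column.
- **Randomization** says "we will prepare the eligible list of participants after household screening, followed by individually randomizing the total participants into control and intervention groups". It does not mention the baseline survey. The Quantitative survey section makes the final eligible list the sampling frame for baseline data collection.
- **Abstract, Methods** suggests the opposite order: "After the baseline recruitment, participants will be randomly assigned to these two arms across the three locations".

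On blinding, the Randomization section says "Researchers will not be blinded to the treatment condition assigned to individual participants". On analysis, the Data analysis plan makes the primary comparison a mixed-effects logistic model with baseline as one of the time points, tests the interaction of time and arm, and calls the unadjusted result causal because assignment is random.

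**The concern.** In a difference-in-differences analysis the baseline is part of the estimate. A baseline completed before allocation cannot depend on arm except by chance. A baseline completed after allocation has no such guarantee.

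Two routes matter here. First, answers may differ by arm if the girl or the interviewer knows the allocation. The outcomes are self-reported, many are sensitive (contraception, consent, refusing sex), and the survey is face to face. Second, participation may differ by arm. Table 2 marks consent again at t1, so on that schedule a girl could decline the baseline survey after her arm is set. The imputation rule in the Data analysis plan is written for girls who miss the follow-up survey, not for girls allocated but never surveyed at baseline.

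The article does not leave the order open for a fuller document to settle. It states the order, in ways that cannot all be right.

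**Working it through.** **1. The passages side by side**

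| Place | Baseline relative to allocation | How clear |
|---|---|---|
| Abstract, Discussion | after | explicit |
| Table 2 | after (allocation at 0, baseline at t1) | explicit |
| Randomization, read with Quantitative survey | consistent with after | inference only; the baseline survey is not named |
| Abstract, Methods | before | suggested; it speaks of recruitment at baseline, not of the survey |

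So two places are explicit, one fits the same order by inference, and one points the other way. The abstract conflicts with itself. The planned numbers agree with each other (3 × 650 = 1,950; 3 × 325 = 975; 2 × 975 = 1,950) and do not settle the order.

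**2. Effect on the estimator**

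Let s be the shift in the encouragement arm's baseline caused by allocation, with follow-up unaffected. On the percentage-point scale:

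DID = (follow-up difference) − (baseline difference) = true effect − s.

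If s = 0 there is no bias, whatever the order. A reporting shift of equal size at both surveys cancels.

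**3. Illustration of size**

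From the article: n = 975 per arm and significance level 0.05, taken as two-sided because the article does not say. Assumed, because the article gives no figures: prevalence p = 0.5, within-girl correlation ρ = 0.3 to 0.5, true effect zero, and s itself. The calculation is a normal approximation on the percentage-point scale; the planned model is logistic, so it shows scale only.

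SE(DID) = √[2 × 2p(1−p)(1−ρ)/n]

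- ρ = 0.3: √(0.7/975) = 0.0268
- ρ = 0.5: √(0.5/975) = 0.0226

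Rejection rate = P(Z > 1.96 − s/SE) + P(Z < −1.96 − s/SE)

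| s | ρ = 0.3 | ρ = 0.5 |
|---|---|---|
| 0 | 0.050 | 0.050 |
| 2 points | 0.116 | 0.143 |
| 5 points | 0.463 | 0.598 |

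Over a wider range (p = 0.2 to 0.5, ρ = 0.3 to 0.7), a 2-point shift gives 0.12 to 0.30 and a 5-point shift 0.46 to 0.95.

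**4. Direction**

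Take s = +2 points in the encouragement arm.

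- ρ = 0.3: s/SE = 0.746. False findings against the game: P(Z > 1.214) = 0.112. False benefit: P(Z < −2.706) = 0.003.
- ρ = 0.5: s/SE = 0.883. False findings against the game: P(Z > 1.077) = 0.141. False benefit: P(Z < −2.843) = 0.002.

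An upward baseline shift therefore produces almost only false findings against the game. A downward shift of the same size reverses the two figures and produces almost only false benefit.

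**The case against.** The strongest reply is that a baseline taken after allocation need not be biased. If it is finished before encouragement starts, and neither answers nor participation depend on arm, the difference-in-differences estimate is unbiased. That stands. A reader might infer that the order written in the article biases every estimate; the documents support only that it can.

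A reader might also infer that baseline interviewers or girls know the arm at the interview. The blinding statement concerns researchers, and no section says what interviewers or girls know at baseline. The article also describes surveyors and program facilitators as separate roles, which makes interviewer knowledge less likely. It does not exclude it.

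The shared t1 column in Table 2 might suggest that encouragement begins before the baseline interview. The arrows can equally be read as an intervention running between the two surveys, and the abstract's Discussion lists baseline before encouragement. Moreover, early exposure could not inflate type I error: a game with no effect cannot move the baseline, and one with an effect would have its estimate attenuated. The table needs clarifying, but it does not show early exposure.

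Finally, it would be too strong to say that the causal claim fails. Assignment remains random under either order. What is at risk is the subtraction of the baseline and, if refusal depends on arm, the comparability of the girls analysed.

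None of this removes the contradiction or supplies the protection that a baseline before allocation gives by design.

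**Conclusion.** The article is inconsistent on a central step of the trial. The abstract's Discussion and Table 2 put the baseline after allocation, the Randomization and Quantitative survey sections together are consistent with that, and the abstract's Methods suggests the reverse.

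The point matters because the primary analysis subtracts the baseline. Any arm-related shift in baseline answers passes into the effect one for one on the percentage-point scale, with the sign reversed. Under the stated assumptions a 2-point shift takes the two-sided type I error from 5% to about 12–14%, in a direction that depends on the sign of the shift. Nothing in the article shows that a shift of this or any size will occur, so these figures describe sensitivity and are not a forecast. The contradiction itself rests on the text alone and needs no assumption.

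**What to change.** State one order in the abstract's Methods, the abstract's Discussion, the Randomization section and Table 2: household listing, consent or assent, completed baseline survey, allocation, encouragement. In Table 2, move the baseline mark to before allocation and show encouragement starting after it. State that only consented girls with a completed baseline are randomised.

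If the baseline must follow allocation, say so everywhere, keep the arm concealed from interviewers and girls until the survey is done, and start encouragement only afterwards.

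The change is one of wording and field sequencing and adds no participants. Its small downside is that allocation waits for baseline completion. It has to be settled before fieldwork, because a baseline untouched by allocation cannot be recovered later.

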## Background

India is home to 253 million adolescents, where every fifth person is between 10 to 19 years [1]. Adolescent girls are facing a range of social, economic, and structural barriers including receiving adequate information on sexual and reproductive health (SRH), menstrual health and hygiene, fertility awareness, and the self-efficacy to seek health services and make choices for themselves. Fifty percent of girls aged 15 to 19 do not use menstrual hygiene products [2]. With limited access to requisite knowledge about menstrual hygiene, methods of contraception, self-care, and well-being, adolescent girls are at high risk of experiencing adverse health and social outcomes such as low educational attainment, lack of career aspirations, forced/early marriages, unintended pregnancy, and gender-based violence [3].

Interventions designed to minimize risks to adolescents include counselling through public health service providers, peer education, and community-based immersion by social development groups. Novel interventions that apply game-based learning to digital media such as mobile phone apps could increase motivation, engagement, and overall sustainability of health behaviours [4]. More recently, interventions that have incorporated serious games [5], through simulation and interactive methods, have gained significant attention from academicians, policymakers, and practitioners. The effectiveness of the next generation of games may be enhanced by building on behavioural change and educational gaming literature (e.g., using role-play and simulation game formats, individual tailoring, offering adaptation in the difficulty of the challenge, and the amount and timing of feedback), as well as human-centric design principles that follow user preferences [6].

Evaluation of a mobile game intervention to disseminate health-related knowledge and information and understanding use of game-based learning approaches to promote SRH, particularly to adolescents in low-income settings, has been limited. Generating evidence to examine causal impact of mobile games on adolescent SRH behaviour, longer-term health outcomes, self-efficacy and autonomy, and more expansive measures of well-being, is essential. Rigorous evaluations of game effectiveness, longer-term follow-up, and using measures of behaviour rather than merely their determinants, is warranted [7].

### Go Nisha Go mobile game

Go Nisha Go™ (GNG) is a role-play, simulation game [8], mobile app that follows the life of a young Delhi-based protagonist, Nisha, as she embarks on a journey of self-discovery and agency. Played across five levels, the game uses an aspirational [9] travel theme that has Nisha visiting the Indian cities of Sikkim, Mumbai, Goa, and Hyderabad, while meeting inspirational women (a scientist, an influencer, a nurse, and a police officer), as part of her internship for a web series production. Hindi is the spoken language of the game and Hinglish (Hindi language written in Latin script) is the script of the game. Thus, the interaction and communication with the game is made effortless [6]. Each level focuses on specific game-based objectives related to menstrual health, fertility awareness, contraception, and consent, scaffolded on outcomes related to negotiation, relationship obligation, health knowledge, and confidence. The game is designed to increase knowledge incrementally (and subsequently the confidence and efficacy to make better choices) through strategically placed ‘nudges’ in the gameplay, trade-offs/rewards, minigames, and direct access to resources such as educational videos and a chatbot. The game does not collect any Personally Identifiable Data (PID), thus protecting players’ privacy.

### Evaluation framework and theory of change (TOC)

The Go Nisha Go (GNG) evaluation framework [10] is underpinned in theoretical frameworks such as the Integrated Model of Behaviour Change [11] and the Fogg Behaviour model [12, 13]. These theoretical models define the innovative intervention used to address knowledge, attitude, self-efficacy, and practice indicators for SRH among girls aged 15 to 19 years.

The TOC [8] informs a robust results framework with the following action-oriented Intermediate Results (IR):IR1: Improved knowledge about SRH care including menstruation, menstrual hygiene, fertile period, and SRH/menstrual management products.IR2: Improved attitudes, confidence, and decision support for managing self-care, family planning, negotiating consensual sex and contraceptive use, and accessing/using DTC products, information, and care.IR3: Improved assertion of self-identity through DTC linkages to career, safety, and personal well-being resources, and improved self-efficacy through linkages (access) to SRH products, information, and care.

In this paper, we describe the study protocol for the implementation of an outcome evaluation (OE) that measures (a) increase of knowledge of select SRH indicators, including fertility awareness, comprehensive contraceptive knowledge among adolescent girls; (b) improved access to SRH information, products, and services via DTC links within the game; and (c) intended behaviour change actions that increase agency and confidence among adolescent girls for successful SRH outcomes.

## Methods

This study protocol paper is aligned to SPIRIT 2013 guidelines [14]. The study is designed as a two-armed individual Randomized Control Trial (RCT) comprising a treatment (encouragement) arm and a control arm.

### Study setting

The study will be conducted in three Indian peri-urban areas of three states—Patna in Bihar, Jaipur in Rajasthan, and Delhi NCR (National Capital Region).

### Selection/eligibility criteria

Eligible participants are unmarried adolescent girls aged 15 to 19 years, living in Patna-Bihar, Jaipur-Rajasthan, and Delhi NCR, able to read Hinglish (Hindi and English hybrid in Latin Script), and who have access to an Android-based device with internet. We will note the demographics of participants who refused to be part of the study, which will be analyzed for participation bias.

### Pretesting of methods and learnings

In preparation for the RCT, we pre-tested the study protocol for feasibility of methodology and implementation guidelines, where we recruited 270 girls to determine which of three modes (in-person surveys, online self-administered surveys, and telephonic interviews) of recruitment could be finalized. For in-person surveys we recruited 120 girls: (n = 40) in Patna, (n = 40) in Jaipur and in (n = 40) Delhi NCR. Similarly, for the telephonic surveys and online surveys respectively, 60 girls each were recruited in total: Patna (n = 20), Jaipur (n = 20), and Delhi NCR (n = 20). We also tested a qualitative tool through in-depth interviews (IDI) with 30 girls in the three cities of Patna (n = 10), Jaipur (n = 10), and Delhi NCR (n = 10).

All participants were recruited from an eligible list of participants after a household survey. The interviews were conducted in a confidential and comfortable space in the participant’s household/community after taking consent for participation in the study.

The pretesting aided in examining the feasibility of the methods and determined that the response rate of in-person interviews (face-to-face) was higher than the other two modes. Refusal to take interviews over the telephone was considerably high. In the online self-administered interviews, many girls opted out, saying they were not comfortable with sharing personal information online. We also found that school examination times interfered with the recruitment of participants, and therefore made plans to conduct the encouragement study after exams. We also pretested creative messages for the encouragement and determined that additional creative messages were needed to motivate participants to not only download the game, but also play all five levels. ﻿The two-armed RCT will now be conducted only through in-person mode of recruitment after exams.

Additionally, to ensure comparison with outcome evaluation data and in-game metrics, we will now ask recruited participants to download a unique six-digit profile code that will be generated at start of gameplay. The profile code from the participant will determine how data from the OE can be matched with the in-game choices of the same player.

### RCT study

#### Sample size

The study proposes recruiting 1,950 participants from three sites: 650 girls each from Patna, Jaipur, and Delhi NCR for in-person interviews. In addition, 60 girls (n = 20 each from Patna, Jaipur, and Delhi NCR) will be recruited purposively from the encouragement arm of 975 participants for qualitative in-depth interviews. During the encouragement design activity, half of the participants (i.e., 325 girls each from Patna, Jaipur, and Delhi NCR) will receive nudges/encouragement to play the game.

#### Recruitment

Eligible participants of the study will be identified by trained surveyors in-person through the eligibility screening process and household listing. Following this, a sampling frame with potentially eligible respondents and their parents (for minor eligible adolescent respondents who are below 18 years) will be approached by the field team for consent and recruitment into the study. A Field Coordinator and Supervisor will monitor this process including the sketching of Primary Sampling Units (PSU) to ensure that mapping and recruitment is done ethically as per standard protocols. The final recruitment of participants will be selected from a household listing in the eligible criteria: unmarried, adolescent girls ages 15 to 19, having their own or shared mobile device with internet access.

#### Randomization

For implementation of the RCT we will prepare the eligible list of participants after household screening, followed by individually randomizing the total participants into control and intervention groups [15]. Randomized participants in the treatment arm will get exposure to the GNG game as part of the encouragement design, while the participants randomly assigned to the control arm will not get any additional encouragement to download or play the game. (See Fig. 1) Researchers will not be blinded to the treatment condition assigned to individual participants [16].

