a = constant.

s and t are study arm and time, respectively.

b_1_ and b_2_ are slopes for the study arm and time, respectively.

b_3_ = treatment effect.

s*t is a dummy variable indicating treatment status.

The significance level of the test will be measured using a p-value < 0.05 (95% level of significance as per the sample size estimation).

The primary comparison of the binary outcomes between intervention groups at baseline and follow-up will use mixed-effects longitudinal logistic regression, with random effects for the individual over time. The baseline will be included as a time point only. A categorical time effect will be used (profile model). A “difference-in-differences” analysis will compare the treatment arms. Statistically, this amounts to testing for an interaction between time and treatment arm in the longitudinal model. Since the treatment assignment is at random, this “unadjusted” analysis will provide a causal effect of the intervention. However, we will also conduct secondary analyses, adjusting for potentially relevant covariates (e.g., age, education, etc.), in addition to time and treatment arm, using backward model selection at the α = 0.15 threshold level. These secondary analyses may improve the precision (power) of estimating the treatment effect and reduce any bias due to random imbalances between arms.

The primary analyses will use an intent-to-treat approach and analyze all subjects according to a randomized group. For subjects missing the follow-up survey, we will impute data from the lower (worse) half of the distribution by the arm (conservative approach). We will also conduct dose analyses, in which we include only those subjects who complete the full intervention. Analyses will use data only for outcomes; (a) increased comprehensive contraceptive knowledge, (b) MHM (c) negotiation and self-efficacy. We will conduct exploratory analyses using outcomes.

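### The Randomization section, read literally, does not secure the 325 encouraged girls per city stated under Sample size; site is in no guaranteed model, and adjusted covariates are chosen by backward selection

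*Protocol article*

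**What the plan says.** All references are to the protocol article.

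- **Sample size:** "The study proposes recruiting 1,950 participants from three sites: 650 girls each from Patna, Jaipur, and Delhi NCR for in-person interviews". It adds that "half of the participants (i.e., 325 girls each from Patna, Jaipur, and Delhi NCR) will receive nudges/encouragement to play the game", and gives the encouragement arm as 975.
- **Randomization:** an eligible list is prepared after household screening, followed by "individually randomizing the total participants into control and intervention groups". No stratification or blocking by city is mentioned.
- **Abstract, Methods:** "participants will be randomly assigned to these two arms across the three locations".
- **Data analysis plan, simple regression:** the difference-in-differences (DID) regression has terms for arm, time and their product.
- **Data analysis plan, primary comparison:** "mixed-effects longitudinal logistic regression, with random effects for the individual over time", tested through the time-by-arm interaction. The plan calls it unadjusted: "Since the treatment assignment is at random, this “unadjusted” analysis will provide a causal effect of the intervention".
- **Data analysis plan, secondary analyses:** covariates, with age and education as the examples, are added to time and arm "using backward model selection at the α = 0.15 threshold level".

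**The concern.** A fixed 325 per city follows only from allocation within each city. One draw over everyone enrolled meets that figure on average and leaves chance differences between cities. The abstract's wording fits either scheme, so it does not settle the matter.

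The analysis has a matching gap. If allocation is balanced by city, the balancing factor belongs in the model, yet neither the DID regression nor the primary model has a site term. The adjusted analyses do not guarantee one either, because only time and arm are fixed and everything else can be dropped.

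The selection rule is a weakness in itself. The plan justifies adjustment by better precision and by correction of chance imbalance. A rule that picks covariates from the outcome data secures neither aim. It can give a different covariate set for each of the 24 indicators in Table 4 (7 + 8 + 9), and the usual standard errors ignore the selection step.

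**Working it through.** **The plan's own figures.** 3 × 650 = 1,950; 650 / 2 = 325; 3 × 325 = 975. They agree with each other and imply 1:1 within each city.

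**What a single draw over all 1,950 gives, with 975 per arm fixed.** The encouraged count in one city is hypergeometric (population 1,950, 975 encouraged, 650 in the city).

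- Mean 650 × 975/1,950 = 325.
- SD = √(650 × 0.25 × 1,300/1,949) = 10.4; exact 95% range 305 to 345.
- P(325 in one given city) = 0.0383. Given that, P(325 in a second) = 0.0442, and the third is then fixed. The product is 0.0017, the same as C(650,325)³ / C(1950,975).
- In 200,000 simulated draws the worst city was off by 10 or more in 63% and by 20 or more in 15%.

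If the arm totals were not fixed either (simple 1:1 randomisation), the SD per city would be √(650 × 0.25) = 12.7. The arm total of 975 would itself be met exactly in only 1.8% of draws.

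**What leaving site out costs if allocation is balanced by site.** The documents give no prevalences, so three sets are assumed, each averaging 50%. For a binary outcome, site R² = variance of the site prevalences / 0.25, and the SE without site divided by the SE with site is about 1/√(1 − R²).

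| Assumed site prevalences | Site R² | SE ratio |
|---|---|---|
| 40/50/60% | 0.027 | 1.014 |
| 30/50/70% | 0.107 | 1.058 |
| 25/50/75% | 0.167 | 1.095 |

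To see which analyses this applies to, two-wave data were simulated with 325:325 per city, a girl-level random intercept of SD 1.3 and an interaction of 0.35 on the log-odds scale (both assumed).

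- DID regression fitted as written to the stacked data: ratios 1.014, 1.058, 1.095.
- Unadjusted endline comparison: 1.013, 1.058, 1.094.
- Within-girl change, a linear stand-in for the primary test: 1.000 in all three cases.
- The mixed logistic model itself (40 simulated datasets per case): 1.0000, 1.0002, 1.0003.

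Stable site levels cancel in the within-girl contrast, so the 1 to 9% applies to the simpler regression and to endline comparisons, not to the primary test.

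**What a pooled draw costs.** With 30/50/70%, the arm difference at endline due to site imbalance is (0.4/975) × (count in the highest city − count in the lowest). That difference in counts has SD √(3 × 10.41²) = 18.0, so the contribution has SD 0.4 × 18.0/975 = 0.0074, or about 0.7 percentage points. It is random with mean zero.

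**Covariate selection.** No arithmetic applies. The rule keeps a covariate only if it passes 0.15 in that outcome's model, so site may be kept for one indicator and dropped for another.

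**The case against.** **The sections may be compatible.** The Randomization section never says that cities are pooled; its wording can mean simply everyone enrolled. Together with 325 per city and the abstract's phrase, it can be read as allocation within city. Fig. 1, to which the section refers, is not shown, and an article commonly leaves strata and blocks to the full protocol. This stands in part: a reader might infer that the trial will miss 325 per city, and the documents do not support that. What remains is that two affirmative statements need to be made to agree.

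**A miss of 10 to 20 girls in 650 does no harm.** Correct. A pooled draw is valid and unbiased, and the exact-match probability measures inconsistency, not damage.

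**The primary test gains nothing from a site term.** Also correct when site levels are stable. A reader might infer that the primary intervals are too wide or that its power suffers; the calculation does not support this. Nor can a power loss be given for the other analyses, since the article states no effect size.

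**The two harms are alternatives.** Chance imbalance arises under pooled allocation, and overstated standard errors under balanced allocation. Only one can apply.

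**Backward selection is confined to secondary analyses, and the covariate list is open-ended.** True: site is not excluded, and different covariates per outcome is something the rule permits rather than something the plan announces. But the selection rule is a stated choice, and it serves the plan's own reasons for adjusting less well than a fixed list.

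**Conclusion.** The point holds as a matter of consistency and modest precision. The Randomization wording does not secure the stated 325 per city: on the literal reading with fixed arm totals, the SD is about 10 girls, the 95% range 305 to 345, and the chance of an exact match in all three cities about 0.2%.

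Leaving out site costs essentially nothing in the primary mixed-model interaction test. If allocation is balanced by site, it overstates the SE by about 1 to 9% in the simple DID regression and in unadjusted endline comparisons. That range rests wholly on assumed site prevalences. Backward selection makes the secondary adjusted results harder to compare across outcomes and leaves their standard errors uncorrected for selection; the size of that effect was not estimated.

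None of this threatens the validity of the randomised comparison.

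**What to change.** 1. **Reconcile Sample size, Randomization and the abstract** by stating that girls are randomised 1:1 within each city's list, 325 of 650. The list exists before allocation, so this means three draws instead of one. Exact 325:325 requires each city to close at 650 and, if permuted blocks are used, a block size that divides 650 (4 does not). If a single pooled draw is intended, describe 325 as the expected number.
2. **Carry site as a fixed effect** in the DID regression, the endline comparisons and, for consistency, the primary model. With three sites this is one categorical term.
3. **Replace backward selection with one prespecified baseline covariate set** for all outcomes, including site (for example site, age and education). The cost is choosing the set before follow-up data are seen.
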